### Outcome Analysis

Based on the primary end points, we will determine whether or not this pilot study is as follows:

Feasible: all feasibility outcomes are met; no protocol modifications are needed,Feasible with modification: all feasibility outcomes are met or can be met with protocol modifications, andNot feasible: Even with protocol modifications, some feasibility outcomes cannot be met.

In terms of statistical analyses for this feasibility study, preliminary analyses will consist of univariate tests to compare clinical and demographic variables of interest. Linear regression analysis will be used to quantify the strength and magnitude of the relationship between the intervention and the coprimary outcomes. Secondary outcomes will be analyzed as continuous measures using generalized linear regression models.

For any missing data where patients do not attend the allocated sessions or do not complete all components of the relevant questionnaires, this will be noted and documented to assess the overall feasibility of this study. Data will not be extrapolated or interpreted for these missing data sets.

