Internet-delivered cognitive behavioral therapy (CBT) for chronic pain, depression, and anxiety is associated with significant reductions in pain disability, symptoms of depression, and pain catastrophizing at 1 year follow-up [7]. Nonetheless, an integrative review [8] concluded CBT research must further address longer-term efficacy (>12 months). This same review highlighted the significant variations in the duration and total dose hours of CBT interventions and delivery methods (remote, group, or individual). Despite variations, existing studies and emergent guidelines support the synergistic effects of pharmacological therapies strategically combined with CBT-based strategies [7].

The primary objective of this trial is to study the effects of concurrent ketamine and CBT for chronic neuropathic pain relief. Biological and neurocognitive factors suggest that concurrent pharmacotherapy and psychotherapy can result in more durable and effective analgesic responses than either intervention alone. Ketamine administration induces physiological changes during and after delivery that result in powerful experiential responses with important psychological and emotional impacts [9]. The physiological changes associated with ketamine therapy are likely to influence important habitual thinking and behavior patterns. Studies suggest that ketamine alters functional brain connectivity, even to the point of disrupting spatiotemporal patterns of neural activity and increasing functional communications between brain regions typically isolated [9].

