### Outcome Measures

#### Primary Outcome

The primary outcome of this pilot trial is to determine the feasibility of a large-scale multicenter trial. Feasibility outcomes will include the following variables, with all thresholds listed in parentheses:

Recruitment success (with the specific aim of recruiting all necessary patients within the first year of the trial period).Adequate consent rate (>30% of eligible patients consent to participate in the study).Percentage of patients who complete all medication and psychotherapy visits (ie, intervention adherence; >90%).Percentage of patients who withdraw from the study (eg, due to side effects or other reasons; <20%).Percentage of patients with incomplete pain intensity and pain interference data at 1 month and stated or ascribed reason (eg, withdrawal due to side effects, loss of follow-up, or missing data; <10%).Rate of adverse outcomes (ie, 0 serious adverse events).

Based on the result for each primary feasibility outcome, we will determine whether the definitive study is feasible as proposed (ie, all feasibility targets are met), feasible with protocol modifications (modifications specified), or not feasible because feasibility targets could not be met even with protocol modifications. These cutoffs, identified in the parentheses above, will help determine whether protocol changes are required before proceeding with a definitive trial.

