#### Secondary Outcome

The secondary outcomes chosen for the definitive trial follow consensus recommendations of core domains that should be addressed in studies examining chronic pain. Information will be collected in these domains as part of the pilot trial using survey-based outcome assessments, either in person during study visits or over the telephone by trained research personnel. The following pain score questionnaires will be used:

Pain intensity on an 11-point (0-10) Numeric Rating Scale.Pain interference on the Patient-Reported Outcomes Measurement Information System (PROMIS-PI) scale.Catastrophic thinking about pain, as measured by the Pain Catastrophizing Scale (PCS).Features of depression, as measured by the Patient Health Questionnaire-9 (PHQ-9).Features of anxiety, as measured by the Generalized Anxiety Disorder-7 (GAD-7).Patient Global Impression of Change Scale (PGIC).

Secondary clinical outcomes will include changes relative to baseline assessment in pain intensity and pain interference at week 20 (4 weeks post-completion of treatment; Figure 1). Scores for all outcomes at weeks 2, 7, 12, 16, and 20 will be compared to baseline scores to assess any progressive additive effects between the treatments. For any patients who withdraw before week 20, their last documented responses will be used as a comparison against baseline data. Patients will be allowed to adjust the dosages of other analgesic medications in conjunction with their primary physician. Analgesic medication use and doses will be tracked at the above time points to assess changes over time. Semistructured interviews will be conducted at 2 points within the study period: at weeks 1 and 20 and after the ketamine infusions (Table 1). The interviews will be audio-recorded to ensure the responses are accurately captured. In-person interviews will be recorded with an encrypted device, and phone interviews will be recorded through the Unity Health Zoom (Zoom Video Communications Inc) recording option. The audio recording files will be saved on St. Michael’s Hospital secure and restricted servers, and the files will be labeled by the study number. The recordings will be transcribed by the research team, and after verifying that the transcriptions are accurate, the audio recordings will be destroyed. Questionnaires will be delivered to patients at prespecified time points, as outlined in the study timeline below.

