This study will inform the development of a larger-scale multicenter RCT. Our results will help inform the sample size calculation to ensure an adequately powered, definitive RCT. We anticipate that the psychotherapy and ketamine protocols developed in this study will be easily replicable and scalable should they show clinical and statistical benefits in the chronic neuropathic pain population. Furthermore, future studies developed by our research team will aim to study longer-term outcomes associated with KAP and the need for ongoing therapy in this patient subset.

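### The planned regression on arm names coprimary outcomes that are never defined, and additive effects are to be judged against baseline in a design with no untreated arm

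*Protocol article*

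**What the plan says.** All references are to the protocol article.

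- **Primary outcome.** The Primary Outcome section states: "The primary outcome of this pilot trial is to determine the feasibility of a large-scale multicenter trial". It lists six criteria: recruitment, consent, adherence, withdrawal, incomplete pain data and adverse outcomes. The Objective in the Abstract and the Aim section also make feasibility primary.
- **Primary decision rule.** The Outcome Analysis section begins with a three-level classification, whose top level reads "Feasible: all feasibility outcomes are met; no protocol modifications are needed". No regression is involved.
- **Regression.** The same section then says "Linear regression analysis will be used to quantify the strength and magnitude of the relationship between the intervention and the coprimary outcomes". Its next sentence gives the secondary outcomes a separate generalized linear regression model. The term coprimary is used nowhere else.
- **Pain outcomes.** The Abstract, the Aim section and the Secondary Outcome section treat pain intensity and pain interference as secondary.
- **Conflicting objective.** The Introduction says: "The primary objective of this trial is to study the effects of concurrent ketamine and CBT for chronic neuropathic pain relief".
- **Additive effects.** Under Secondary Outcome, scores at weeks 2, 7, 12, 16 and 20 "will be compared to baseline scores to assess any progressive additive effects between the treatments".
- **Arms.** Ketamine alone (Arm 1), CBT/MM alone (Arm 2) and both (Arm 3). No arm receives neither.

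**The concern.** A regression on arm needs a dependent variable, and this one has none that a reader can identify. If the coprimary outcomes are the feasibility criteria, two of the six have no arm to regress on. If they are pain intensity and interference, the analysis text promotes two secondary outcomes to primary status, and the Introduction's statement of the objective would support that reading. An analysis plan written from this text could go either way, in a 30-patient study that says it is not powered for clinical effects.

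The second part concerns interpretation. Improvement since baseline may occur in all three arms for reasons unrelated to treatment, and entry requires a mean pain score above 3. If such improvement is read as treatments adding to one another, the pilot would appear to support the combination on evidence that cannot do so.

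**Working it through.** The protocol gives no power, alpha, SD or effect size for these analyses, so there is no figure of its own to reproduce. The check has three parts.

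**1. What could the coprimary outcomes be?**

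- *Feasibility criteria.* Table 1 places consent at screening and randomization at week 1. Recruitment within the first year is a trial-level quantity, and the consent criterion, "Adequate consent rate (>30% of eligible patients consent to participate in the study", has eligible patients as its denominator. Neither has an arm. Adherence, withdrawal and incomplete data are yes/no for each randomized patient, and adverse events are counted per patient. These four can be compared by arm, though a linear model with normal-theory inference suits them poorly at this sample size.
- *Pain intensity and interference.* These have an arm and are continuous, so the model would work. But they are labelled secondary, and the next sentence of the same section gives secondary outcomes another model.

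Neither reading fits the text as it stands.

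**2. What can three arms identify?**

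Let μ0 be the mean change with neither treatment, k the ketamine effect, c the CBT/MM effect and kc their interaction.

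- Arm 1 mean = μ0 + k
- Arm 2 mean = μ0 + c
- Arm 3 mean = μ0 + k + c + kc

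Three means for four parameters give a design matrix of rank 3. The interaction kc, and k and c individually, are not estimable. Two contrasts are:

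- Arm 3 − Arm 1 = c + kc
- Arm 3 − Arm 2 = k + kc

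An invented example shows the limit:

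| | μ0 | k | c | kc | Arm 1 | Arm 2 | Arm 3 |
|---|---|---|---|---|---|---|---|
| Purely additive | 0 | −1.5 | −1.0 | 0 | −1.5 | −1.0 | −2.5 |
| Synergistic | −0.5 | −1.0 | −0.5 | −0.5 | −1.5 | −1.0 | −2.5 |

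The arm means are identical, so no analysis of these arms separates the two cases. Each mean change from baseline also contains μ0 (natural course and regression to the mean). In the synergistic row, 0.5 of every arm's improvement is not treatment at all. The two between-arm contrasts cancel μ0.

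**3. Precision of the contrasts that can be estimated.**

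Assumptions: 30 patients split 10 per arm (the allocation ratio is not stated), common SD, two-sided 95% CI, and residual SD pooled over three arms (27 df).

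- Unadjusted week-20 difference: half-width = t(27, 0.975) × √(2/10) = 2.052 × 0.447 = 0.92 SD. The normal approximation gives 1.96 × 0.447 = 0.88 SD.
- Baseline-adjusted against change score: with baseline to week 20 correlation r, the variances are proportional to 1 − r² and 2(1 − r). The ratio of CI widths is √[(1 − r²)/(2(1 − r))] = √[(1 + r)/2].

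| r (assumed) | Ratio | CI narrower by |
|---|---|---|
| 0.3 | √0.65 = 0.806 | 19% |
| 0.5 | √0.75 = 0.866 | 13% |
| 0.7 | √0.85 = 0.922 | 8% |

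These ratios ignore the one degree of freedom spent on the covariate.

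**The case against.** The strongest reply is that this is largely a labelling defect. Several stronger readings are tempting, and the document does not support them.

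- *The primary outcomes receive an inapplicable main analysis.* They do not. Their analysis is the feasibility classification, which works whatever coprimary means.
- *Feasibility outcomes cannot be regressed on arm.* This is true only of recruitment and consent. The other four criteria, such as "Percentage of patients who complete all medication and psychotherapy visits (ie, intervention adherence; >90"%, exist for each randomized patient, and the Discussion intends to compare feasibility across arms. Least squares of a 0/1 outcome on arm even returns the differences in proportions; the weakness lies in the inference.
- *Pain is to be tested within each arm, many times over.* The Secondary Outcome section does not say within arm and states no significance rule. The Abstract's Objective compares the combination with each single treatment, and the Hypothesis section expects the greatest reduction in the combination arm. A randomized between-arm comparison of change is not biased by regression to the mean. Counting multiple tests would therefore criticise a procedure that the protocol does not describe.
- *The design cannot show any added benefit.* If additive means benefit over each single treatment, the two contrasts above identify it. The protocol also proposes to assess such effects; it does not claim them.
- *The observed pilot effect will size the next trial.* The Discussion says only "Our results will help inform the sample size calculation to ensure an adequately powered, definitive RCT".

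Choice of covariates is normally left to an analysis plan, so the lack of a stated baseline covariate is not a fault here. Baseline adjustment is offered as part of the repair.

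All of these replies stand. They leave untouched the undefined outcome, the conflicting primary objective, and the sentence that draws additive effects from comparison with baseline.

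**Conclusion.** The point holds in limited form. The regression sentence has no defined outcome, and the Introduction contradicts the Objective, Aim and Primary Outcome sections on what is primary. Comparison with baseline is the wrong basis for additive effects, and three arms without an untreated cell cannot separate additivity from synergy. That last limit follows from the design and rests on no assumption.

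The combination's benefit over each single treatment is estimable, but imprecisely: about ±0.92 SD unadjusted, given the assumed 10 per arm. The gain from baseline adjustment, 8% to 19% over change scores, depends on the assumed correlation. This should be corrected, but the feasibility decision itself is not invalidated.

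**What to change.** 1. Replace the coprimary sentence in Outcome Analysis. Report feasibility outcomes as counts and proportions with exact 95% CIs, overall, and by arm only for those that arise after randomization.
2. Label week-20 pain intensity and PROMIS-PI as secondary throughout. Estimate Arm 3 vs Arm 1 and Arm 3 vs Arm 2 differences with 95% CIs, from a linear model with arm as a factor and the baseline score as covariate.
3. List the Numeric Rating Scale among the baseline and follow-up assessments. The Secondary Outcome section names it, but Table 1, Baseline Data and Follow-Up Data omit it, and the model in step 2 needs it.
4. In Secondary Outcome, replace the wording on progressive additive effects with these two contrasts.
5. Align the Introduction's primary objective with feasibility.

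The cost is wording and slightly more analysis, and the additive-effect language is given up. The article reports that recruitment had not begun as of November 1, 2023, so on this document the changes could be made before any patient data existed.

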### Study Status As of Date

As of the current date, November 1, 2023, the study has not started to recruit patients.

## Discussion

It is hypothesized that concurrent pharmacotherapy and psychotherapy have combined effects on the analgesic response. In addition to ketamine’s anesthetic-analgesic properties, it also uniquely alters the individual’s level of consciousness at variable doses. Some researchers posit that the therapeutic experience of psychotherapy may be augmented by ketamine’s alteration of conscious awareness [10]. As demonstrated by this systematic review, few studies have examined ketamine-assisted psychotherapy (KAP) for chronic neuropathic pain. RCTs have not been published on this topic. In addition, there appears to be wide variability in the indication, dosage, and patient treatment setting, such that the current literature is inconclusive.

The 3-arm design allows us to compare the feasibility of KAP with ketamine alone and CBT/MM. We will track feasibility outcomes, including recruitment rate and adverse event rate, to estimate the acceptability of this intervention compared to controls. There are also limitations to this study. Due to the participatory nature of CBT/MM, we are unable to blind patients and the research team to patients’ assigned interventions. To mitigate this, the outcome assessors will be blinded to minimize bias, and we will request and report their “best guess” estimate of each patient’s assigned intervention at the end of the study. We also recognize that there may be different patient outcomes based on the mode of CBT/MM delivery. Patients in arm 1 receiving ketamine alone will have no CBT/MM as part of the trial design. Patients assigned to CBT/MM alone (Arm 2) will be receiving their intervention sessions remotely rather than in-person for 16 weeks. Patients in Arm 3 will be receiving ketamine on weeks 2, 7, and 12 and in-person CBT/MM at this time. They will also be involved with remote CBT/MM sessions from weeks 1 to 16 (except for weeks 2,7, and 12). This hybrid intervention will allow us to collect data on the feasibility of in-person versus remote psychotherapy for this patient population.

This study will inform the development of a larger-scale multicenter RCT. Our results will help inform the sample size calculation to ensure an adequately powered, definitive RCT. We anticipate that the psychotherapy and ketamine protocols developed in this study will be easily replicable and scalable should they show clinical and statistical benefits in the chronic neuropathic pain population. Furthermore, future studies developed by our research team will aim to study longer-term outcomes associated with KAP and the need for ongoing therapy in this patient subset.

## Appendix

Multimedia Appendix 1 Peer review report from the Canadian Pain Society in partnership with the Pfizer Early Career Investigator Award.

## Abbreviations

CBT: cognitive behavioral therapy
CONSORT: Consolidated Standards of Reporting Trials
GAD-7: Generalized Anxiety Disorder-7
KAP: ketamine-assisted psychotherapy
MM: mindfulness and meditation
PCS: Pain Catastrophizing Scale
PGIC: Patient Global Impression of Change Scale
PHQ-9: Patient Health Questionnaire-9
PROMIS-PI: Patient-Reported Outcomes Measurement Information System
RCT: randomized controlled trial
REDCap: Research Electronic Data Capture
